### Study design

HABVIA is a parallel-group controlled trial evaluating heat adaptation options in four sites, one urban and one rural low-income community each in Ghana and South Africa (SA), respectively. Participants will be assigned to intervention or control group using 1:1 block randomisation per site, with an equal distribution of male/females. An automated, computer-generated algorithm will be used for randomisation. Due to the logistical constraints of implementing adaptations in low-income settings, a building verification survey will be conducted to identify residences where the passive cooling interventions cannot be feasibly implemented. These participants will be automatically assigned to the control group and receive an alternative adaptation at the end of the study. Due to the nature of the interventions, participants and researchers will not be blinded to the intervention allocation. There are no pre-defined specific criteria for discontinuing the allocated interventions, but reasons for withdrawal will be tracked and reported in subsequent publications and taken into consideration for analysis.

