**Fig. 2 Fig2:**
[figure not shown]
Schedule of enrolment, interventions, and assessments

The measurement of health outcomes will occur over three consecutive hot seasons, (November to March) with one baseline collection during the 2023 - 2024 hot season and two subsequent post-intervention data collection periods (2024 - 2025 and 2025 - 2026). The interventions will be identified by the study team and presented to the participants during a series of workshops following the baseline measurements in year 1. The adaptation will be implemented following the baseline data collection in year 1, and prior to the start of year 2 hot-season data collection period. For each hot season monitoring period, participants at each site will be grouped into six equal groups of *n*= 10 and monitored for three non-consecutive one-week periods, over 16-week hot season. We have accounted for approximately 4-weeks of suspended research activities during December and January months due to local holidays (Fig. 3). The 7-day health measurement period will include an initial clinic visit (lasting approximately 3 hours) followed by six consecutive 24-hour periods of off-site physiological data acquisition.

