**Fig. 3 Fig3:**
[figure not shown]
Measurement schema for physical health data collection over three hot seasons. There will be 60 subjects in each site, 30 intervention and 30 control. These will be split into 6 subgroups, each of which is monitored over three 7-day periods, evenly spaced over the hot season

Throughout the 16-week hot season, indoor temperature and humidity data will be recorded continuously, while external climate data will be collected continuously throughout the year with the data being provided to the research team by various meteorological agencies, supplemented by project installed weather stations (also see Environmental data, below).

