### Design and implementation of heat adaptation Interventions

At each study site, we will implement experimental heat-adaptation building modifications. The selection of these interventions will be informed by (i) findings of a scoping review of heat adaptations for homes which is currently being undertaken, (ii) local knowledge on heat stress conditions and potential adaptations; and (iii) assessment of affordability - critical to the scalability of interventions in low-income contexts, - technical feasibility, and social acceptability. By ensuring that the adaptations are appropriate and feasible in each context, we hope to establish early project buy-in from community and wider stakeholders such as local policy makers and governmental organisations, ultimately supporting climate resilience investments.

A series of workshops will be held prior to the intervention implementation and subsequently between each measurement period to obtain feedback and inform modifications. The workshops will include explanatory engagement around the passive cooling interventions. The purpose of which is to: 1) collate opinions, feedback, and gauge community buy-in, 2) build knowledge capacity of community residents around different adaptation options, 3) explore potential secondary and/or alternative adaptation options, and 4) to provide an equal and equitable platform for different stakeholders to share knowledge. Qualitative data from post-implementation workshops will inform assessments of the mechanisms of impact, based on United Kingdom Medical Research Council guidance for the evaluation of complex interventions [48]. This will include qualitative insights into intervention preferences and acceptability, as well as the wider socio-economic benefits and trade-offs that arise from the adaptations.

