### Data analysis

For the statistical analysis, means and standard deviations will be presented for continuous variables; medians and interquartile ranges will be reported for continuous variables with asymmetrical distributions. Continuous variables with a small number of ordered categories, as well as all nominal variables, will be described with counts and percentages.Objective 1. The effect of ambient outdoor and indoor temperature on physiological health outcomes (primary: sleep; secondary: core body temperature, hydration) will be assessed both cross-sectionally and longitudinally using a univariable and multivariable generalized linear mixed model. For the multivariable model we will adjust for environmental conditions (humidity, cloud cover, wind speed, precipitation); health covariates (body composition, blood pressure, physical activity, glucose); participant characteristics (sex, age); household characteristics (roof and wall type; size) as well as differences between sites (country, rural vs. urban).Objective 2. The impact of the interventions will be tested in phases, first the association between intervention exposure and night-time indoor temperature, adjusting for household characteristics, site and intervention type. Secondly, the association between intervention exposure and sleep, our primary outcome as well as secondary physical and mental health outcomes. The mediating effect of night-time indoor temperature on this association will be investigated, while adjusting for the covariates described under Objective 1). In addition to this, structural equation modelling (SEM) will be used to produce a pictographic representation of a-priori determined relationships between the variables of interest. It does this by estimating path equations simultaneously allowing for the calculation of direct, indirect and total effects. For missing data, we will explore different imputation methods and run sensitivity analyses to explore whether participants lost to follow-up differ when compared to those who completed the study measurement periods.Objective 3. Qualitative data analysis will be done in parallel with the community engagement workshops and Focus Group Discussions, allowing emerging analysis to shape subsequent implementation and data collection procedures. The analysis will answer process evaluation questions and draw on various qualitative methods including but not limited to reflexive thematic analysis and codebook analysis. A qualitative analysis software (such as MAXQDA) will be used by the investigators to facilitate coding, data management, and data interpretation.

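### In the Objective 2 indoor-temperature model, adjusting for intervention type aliases with intervention exposure, so the single intervention coefficient is not estimable or describes only the reference type

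*Protocol article*

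**What the plan says.** The Protocol article, Data analysis, Objective 2, tests the interventions in phases. The phase at issue takes intervention exposure as the predictor and night-time indoor temperature as the outcome, "adjusting for household characteristics, site and intervention type". The second phase relates intervention exposure to sleep and the secondary health outcomes and examines mediation by night-time indoor temperature, "while adjusting for the covariates described under Objective 1".

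Other sections fix what type can mean:

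- **Study design:** "Participants will be assigned to intervention or control group using 1:1 block randomisation per site". Where installation is not feasible, participants are "automatically assigned to the control group and receive an alternative adaptation at the end of the study".
- **Fig. 3 caption:** "There will be 60 subjects in each site, 30 intervention and 30 control".
- **Design and implementation of heat adaptation Interventions:** "At each study site, we will implement experimental heat-adaptation building modifications". The modifications are to suit each local context. The number of types and how they are spread over homes are not given.
- **Research procedures (text under Fig. 2):** "The adaptation will be implemented following the baseline data collection in year 1, and prior to the start of year 2 hot-season data collection period".

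The article does not say what value of intervention type a control home takes, or in what form type enters the model.

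**The concern.** Intervention type is not a background characteristic that both groups share. It subdivides the intervention group: a home with a type is an intervention home, and a home without one is a control. Entering type beside exposure asks for the effect of having an intervention while holding fixed which intervention the home has, and no control home can supply that comparison.

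The failure can be silent. A program that resolves the redundancy by dropping a column still prints a coefficient labelled intervention, and a reader would take it for the overall cooling effect. Lowering night-time indoor temperature is itself part of Objective 2, and this model is its first test. Phase 1 could then report the cooling achieved by one type while phase 2, which has no type adjustment, reports the health effect of all types together. The two results would not describe the same intervention, although the plan presents them as successive steps.

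**Working it through.** The plan gives no figure for this model to reproduce. Its sample size of 24 per group does not enter the argument.

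**Inputs.** Four sites (Setting), each with 30 intervention and 30 control participants (Fig. 3 caption), so 240 rows. One participant per home and one value per home are assumed for the algebra. Household covariates are left out because they do not remove the redundancy.

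**Step 1: the identity.** Let A = 1 for an intervention home and 0 for a control. Let T_k = 1 if the home has type k, with every T_k = 0 for controls. Each intervention home has exactly one type, so T_1 + ... + T_K = A in every row. The columns are linearly dependent for any K.

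**Step 2: rank check.** Columns = intercept (1) + A (1) + site (3) + type (K).

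| Assumed layout of types | Columns | Rank | Coefficient of A estimable? |
|---|---|---|---|
| Three types | 1+1+3+3 = 8 | 7 | No |
| One type per site | 1+1+3+4 = 9 | 8 | No |
| One type per country | 1+1+3+2 = 7 | 6 | No |
| A single type overall | 1+1+3+1 = 6 | 5 | No |

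**Step 3: what software would print.** Take noise-free data with three types, equally frequent in every site, and assumed effects of -1, -2 and -3 °C. The average effect is (-1 - 2 - 3)/3 = -2.

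- Type 1 as reference: coefficient of A = -1.
- Type 2 as reference: -2.
- Type 3 as reference: -3.
- All columns kept, minimum-norm solution: -1.5.

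The data and the fitted values are the same each time; only the coding differs. The three type-versus-control effects, and hence the -2, can be recovered from any of these fits as contrasts.

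**Step 4: codings that avoid or restore the aliasing.**

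| Coding | Columns | Rank | Overall or exposure effect estimable? |
|---|---|---|---|
| Type removed | 1+1+3 = 5 | 5 | Yes, -2.0 in the example |
| Type nested in the intervention arm, sum-to-zero | 1+1+3+2 = 7 | 7 | Yes, -2.0 in the example |
| Type as a site attribute given to both arms | 1+1+3+3 = 8 | 5 | Yes, but type is redundant with site |
| Baseline season modelled, exposure = arm × post, type a time-fixed label | 1+1+2+3+3 = 10 | 10 | Yes |
| As above, but type switched on only after installation | 10 | 9 | No |

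**Step 5: precision of the reference-type coefficient, under assumed layouts.** With equal residual variance, SE is proportional to √(1/n₁ + 1/n₀).

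- One type per site: 30 v 30 in one site against 120 v 120 overall. √[(1/30 + 1/30)/(1/120 + 1/120)] = √4 = 2.
- Two equal types in a site: 15 v 30 against 30 v 30. √[(1/15 + 1/30)/(1/30 + 1/30)] = √1.5 = 1.22.

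**The case against.** The strongest defence is that the article gives a list of covariates, not a model equation, and that parameterisation belongs in an analysis plan that is not shown. The exposure could be time-varying, because there is one season before installation and two after, and a time-fixed type label would then leave the exposure effect estimable. This stands in part: aliasing follows from the plainest reading, not from every possible one. It does not remove the point. The article names the adjustment without choosing any coding that makes it harmless. The site-level reading makes type redundant with site, which is already listed. The longitudinal reading fails again if type starts at installation, as exposure does.

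A reader might also infer three stronger things, which the documents do not support.

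- **That the intervention effect is lost altogether.** It is not. Only the single coefficient is lost; type-specific effects and their average remain estimable from the same data.
- **That the sleep and mediation results are affected.** The covariates named there are the Objective 1 list, which does not contain type. The phases are ordered, but no rule makes the second depend on the result of the first.
- **That the trial loses precision by a factor of 2 or 1.22.** Those ratios rest on layouts the article does not state. They compare one type's effect with the average over types, so they do not measure a loss of precision for the overall effect.

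**Conclusion.** The concern holds in a limited form. Taken literally, the stated adjustment makes the single intervention coefficient in the night-time indoor-temperature model not estimable, or makes it the effect of whichever type is the reference. This rests on two conditions: control homes have no type during measurement, which follows from the Study design section, and type enters as an ordinary factor beside exposure, which is the natural reading of the list.

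How far the printed value departs from the overall effect depends on how much the types differ, and the article gives no figure for that. The spread from -1 to -3 °C is an illustration with assumed effects. If only one type were used throughout, the two columns would be identical, and dropping the type column would leave the correct overall effect. With several types, the result depends on coding. The problem is confined to this one model.

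**What to change.** Change the phase 1 sentence in one of two ways.

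1. Delete intervention type from the adjustment list. Estimate the overall intervention-versus-control effect with site and household characteristics recorded before installation, so that the adjustment cannot absorb the building modification itself.
2. Keep type but nest it within the intervention arm, for example as sum-to-zero deviations, and name the overall contrast to be reported. State whether the average weights types equally or by their frequency; the two agree only when types are equally common or equally effective.

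In either case, report type-versus-control effects within site from a separate model. Label comparisons between types as non-randomised, because the article describes allocation to intervention or control only. The overall contrast should not be called purely randomised either, since homes where installation is infeasible are placed in the control group.

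The cost is one line of protocol or analysis-plan wording, with no new data and no change to the sleep model. It is best settled before outcome analysis, so that the reported effect cannot depend on a coding choice.

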
### Monitoring

An independent advisory committee has been appointed to provide project oversight. The committee is comprised of experts in human physiology, climate science, biostatistics, and investigators with expertise in clinical trials methodology. The role of the committee is to advise the research team with regards to the following criteria: (i) Study design to ensure participant safety, study conduct and progress, and (ii) recommendations regarding the continuation, modification and termination of the randomized controlled heat adaptation trial. The committee will meet annually throughout the study duration to review adherence to the protocol, performance of individual centres, and data quality and completeness.

### Ethics approval and dissemination

This protocol has been approved by the Ethics Committee and/or Institutional Review Board of each of the participating institutions (Human Research Ethics Committee, University of Cape Town (reference: 469/2023); Kwame Nkrumah University of Science and Technology Committee on Human Research Publication and Ethics (reference: CHRPE/AP/761/23); University of Ghana Noguchi Memorial Institute for Medical Research Institutional Review Board (reference: 024/23–24). The ethical review board will be notified of any protocol amendments that require their approval, and subsequently reported to all research staff and participants.

Written informed consent will be obtained for each participant enrolled in HABVIA. Informed consent documents as well as the clinical and non-clinical data collections will be conducted in the predominant local language of each area: Twi (Nkwantakese); Ga and Twi (Ga-Mashie); iXhosa (Khayelitsha), and Venda (Thoyondou). Project investigators and staff will be trained in research ethics, good clinical practice, and study procedures, and will thereby be equipped to explain the study in detail to all participants, review the informed consent documents, and answer any questions that may arise.

A series of cohort feedback meetings will communicate the study findings to participants and the community. Results of the project will be submitted to peer-reviewed journals and presented at both national and international conferences. Our data sharing policy will be included on our project website and highlighted at research talks. In the final year of the project, the HABVIA team will publish a short article describing the dataset in an open access publishing platform to maximise discoverability and promote reproducibility, transparency and impact.

## Discussion

Despite high vulnerability to heat-related health risk, few robust evaluations of the environmental, health and socio-economic outcomes of heat adaptations in real-world settings have been done in Africa. Indicating a dire need for reliable heat-health data and heat adaptations that are acceptable and feasible in local contexts. By addressing these gaps using extensive physiological measures, linked to environmental changes, the knowledge generated through HABVIA may help to inform policy to support the effective implementation of heat adaptations in sub-Saharan African settings, where they are sorely needed.

The controlled trial described in this protocol will explore whether passive cooling interventions impact on indoor ambient temperatures, particularly at night, and the extent to which they affect sleep quality and subsequent health outcomes. The limitations of this study include blinding issues, as it is not feasible to blind either participants or researchers to the intervention due to the highly consultive nature of the research as well as potential selection bias due to the leveraging of on-going cohorts. The study design is otherwise optimized for both internal and external validity by staggering monitoring periods, measuring potential confounders across health, climate and infrastructure, and by comparing group differences at both the cross-sectional and longitudinal endpoints.

As global warming progresses so will the need to build local capacity to respond and adapt to heat-related health issues in Africa. HABVIA aims to contribute to this by providing a multidisciplinary platform for climate-health research, education, and policy. In addition, the study’s commitment to community engagement for the design and implementation of the intervention, and the resulting mixed-methods approach, will allow for in-depth interpretation of the intervention outcomes and improve relevance and acceptability. Ultimately, the impact of these interventions will depend on uptake, by using locally sourced materials and generating site specific climate and social data that considers baseline health profiles, where pre-existing conditions may make people more vulnerable to heat stress, HABVIA is working towards tailored solutions for multi-vulnerable communities. This can also provide a framework for intervention development in future climate-related studies.

### Trial status

This clinical trial is registered with the Pan African Clinical Trials Registry (PACTR), trial ID PACTR202401521630856, version 1. Retrospectively registered on January 12, 2024. The research activities commenced in November 2023, with participant recruitment starting in December 2023 and concluding in September 2024. Research activities are planned to continue until March 2027. This version refers to version 1 (12^th^ January 2024) of the approved protocol.

## Data Availability

No datasets were generated or analysed during the current study.

## Abbreviations

AWS: Automatic Weather Station
BIA: Bioelectrical Impedance Analysis
CPM: Counts Per Minute
HABVIA: Heat Adaptation Benefits for Vulnerable groups In Africa
PACTR: Pan African Clinical Trials Registry
SSA: Sub-Saharan Africa
SA: South Africa
SAWS: South African Weather Services
UKRMRC: United Kingdom Medical Research Council
